**Outcome evaluations**								
Post-op opioid use					x	x	x	x
VAS-pain with movement	x		x	x	x	x	x	x
VAS-pain at rest	x		x	x	x	x	x	x
KOOS JR	x						x	x
PROMIS-29	x						x	x
Clinical anchors							x	x
Adverse events			x	x	x	x	x	x

The analysis for the primary outcomes will be by intention-to-treat (ITT). All subjects will be analyzed according to randomization status, regardless of the actual treatment received, compliance with therapy, or adherence to the study protocol. For the primary study aim, we will compare the mean difference in postoperative opioid consumption between the placebo and control groups using generalized linear models (GLM) with a Gaussian family specification, assuming the data are normally distributed. If the data are not normally distributed, we will specify a more appropriate distribution based on a visual evaluation of the data using histograms. We will also use GLM to examine the relationship between treatment and outcome at each time point at which outcomes are measured. Last, for outcomes obtained at multiple time points, we will model the effect across all time points using a multi-level mixed effects model to account for repeated measures. Confounders will be defined as variables, which, when added to the model, alter the effect estimate by > 15%. Potential a priori confounders include body mass index (BMI), sex, age, race, and American Society of Anesthesia (ASA) grade. A *p*-value of < 0.05 will be considered statistically significant.

In addition to ITT analysis, per-protocol and sensitivity analyses will also be conducted. The per-protocol analysis will include only those participants who were protocol-adherent, as defined by their having received all assigned treatments and completed all follow-up visits. The sensitivity analyses will aim to identify potential sources of bias or uncertainty using various imputation methods.

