There are 2 prior studies which can be used to estimate sample size for the proposed trial. The first was published by Wadhwa et al. in 2001 [26] and the second by Entezary et al. in 2013 [27]. Entezary et al. provides data that is consistent with a more conservative approach, as they used a much lower dose and investigated dextromethorphan for postoperative pain following arthroscopy–an intervention that results in relatively less pain than TKA. Using the smaller effect size from Entezary et al. (*μ* =  − 2.4, *σ* = 5.4) and standard methodology to compare the means using the T statistic with a non-centrality parameter [28, 29], a sample size of 160 patients (80 patients per group) would give 80% power to detect a difference in postoperative opioid consumption with a two-sided Type I error rate of 0.05. In contrast, using the same methodology for the study published by Wadhwa et al. yields a standardized effect size of 0.53, which corresponds to a sample size of 112 patients (56 patients per group). Given these estimates, we plan to recruit a total of 160 patients, which can accommodate 5–10% dropout. However, it should be noted that even if 5–10% of patients are lost to follow-up, the planned recruitment remains conservative. This is because the high doses used by Wadhwa et al. may not have necessarily increased the effect size in their study. In fact, it is possible that the larger dose used by Wadhwa et al. actually negatively impacted their effect size (by increasing adverse events), but these negative effects may have been offset by the fact that TKA is markedly more painful than knee arthroscopy.

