### Assignment of interventions

Randomization will be conducted according to a central computerized randomization schedule (randomizer.at, from Medical University Graz, Austria; Url: http://www.randomizer.at/) with a 1:1 treatment allocation ratio and no stratification factors. The randomization method will be permuted blocks. Blocks of four were used to ensure equal numbers of subjects in each group. A separate investigator that is not involved in the recruitment, treatment, or assessment of participants will generate the allocation sequence and assign participants to the treatment or control group accordingly. Participants and investigators responsible for recruitment and treatment will be blinded. Treatment will be immediately and permanently discontinued and clinical staff will be unblinded if participants experience one or more of the following adverse events thought to be at least possibly related to study treatment: visual hallucinations, delusions, agitation, stupor, coma, respiratory depression, seizures, or any sign of serotonin syndrome.

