To date, Wadhwa et al. remains an outlier in that it is the only randomized controlled trial to report more frequent adverse events (specifically, transient nausea) in dextromethorphan-treated patients. Unsurprisingly, Wadhwa et al. is also an outlier with respect to dose, as the authors determined the minimum tolerated dose (MTD) to be 200 mg when administered every 8 h [26]. Most trials to date have used doses between 30 and 60 mg when administering dextromethorphan at multiple timepoints [23]. Multiple trials investigating dextromethorphan for postoperative pain have dosed patients with ≥ 60 mg [24, 25, 27, 37–42] or repeated dosing multiple times postoperatively [26, 39, 40, 43, 44], all of which have found improvement or no difference in the frequency of adverse events. Therefore, in the present trial, it was decided to dose patients at 60 mg preoperatively, followed by 30 mg at 8 and 16 h postoperatively, which correlates to the upper end of what has been used in most studies to date, while still being well-below the MTD reported by Wadhwa et al. This dose and duration between repeated doses is also consistent with known pharmacokinetics. For example, at the typical adult dose of 30 mg PO every 4 h, dextromethorphan has an onset of action of 15–30 min and a duration of action of 5–6 h [18]. Serum levels have been shown to peak approximately 2.4 h after a 2.5 mg/kg test dose [45], with a roughly 2-h delay in analgesic effect in relation to peak concentration [22].

The dosing of dextromethorphan is a non-trivial question, particularly in the context of inter-patient metabolic differences. Dextromethorphan undergoes rapid and extensive first-pass hepatic metabolism via cytochrome P450 2D6 (CYP2D6)-mediated O-demethylation to form the active metabolite, dextrorphan [16, 46]. The mean maximum plasma concentration of dextromethorphan and dextrorphan increases linearly with dose [47] and the elimination half-life is between 3 and 4 h [47]. Importantly however, four different metabolic groups have been described in the literature: ultrarapid, extensive, intermediate, and poor metabolizers. Roughly 90% of individuals are considered “extensive metabolizers,” while most of the remaining population are “poor metabolizers” [13]. The median half-life of dextromethorphan between these two groups differs widely, with the median dextromethorphan half-life in extensive metabolizers being 2.4 h and median half-life of poor metabolizers being 19.1 h [46].

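### Screening VAS, KOOS JR and PROMIS-29 are collected but not named as covariates, and the VAS mixed model does not say whether acute and late visits share one effect

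*Protocol article*

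**What the plan says.** All references are to the protocol article, Methods, Participants, interventions, and outcomes, unless stated otherwise.

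- **Schedule (Table 1).** VAS at rest and with movement is taken at screening, at 8, 16, 24 and 48 h, at week 6 and at 3–6 months. KOOS JR and PROMIS-29 are taken at screening, week 6 and 3–6 months only.
- **Outcome definition.** The text before Table 1 puts the secondary pain outcome at 6, 12, 24 and 48 h.
- **Per-visit analysis.** "We will also use GLM to examine the relationship between treatment and outcome at each time point at which outcomes are measured".
- **Repeated measures.** "for outcomes obtained at multiple time points, we will model the effect across all time points using a multi-level mixed effects model". The article gives no treatment-by-time term and no restriction of visits, and excludes neither.
- **Covariates.** A variable counts as a confounder if adding it alters the effect estimate by more than 15%. The potential a priori candidates are BMI, sex, age, race and ASA grade. Baseline physical function, anxiety, depression, fatigue and sleep disturbance appear only in an exploratory aim on differential response.
- **Randomization (Assignment of interventions).** Allocation is "with a 1:1 treatment allocation ratio and no stratification factors", so the design does not balance baseline scores either.

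**The concern.** Two features of the secondary analyses fit poorly with the data being collected.

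First, the screening value of a score is usually among its strongest predictors at follow-up, and here it is already in hand. A change-in-estimate rule suits observational data. In a randomized trial a baseline score does not confound in expectation; its value is that it removes residual variance, which the rule does not look at. Whether it enters is therefore decided by chance imbalance, after the data are seen.

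Second, the intervention is short: a preoperative dose and two more by 16 h, with "the median dextromethorphan half-life in extensive metabolizers being" 2.4 h (Discussion). If one treatment effect is fitted to VAS over all follow-up visits, the result is an average of early analgesia and pain at 3–6 months. These are different questions, and an effect confined to the first 48 h would be diluted.

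At stake are the precision of the patient-reported secondary outcomes and the meaning of the repeated-measures pain result.

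**Working it through.** **1. The plan's own figure.** Inputs: difference 2.4, SD 5.4, "a two-sided Type I error rate of 0.05", 80% power. Standardized effect d = 2.4/5.4 = 0.444. Per group, n = 2(1.960 + 0.842)²/0.444² = 79.5, so 80. The noncentral t gives 80.4 per group, and 79.8% power at 80. The stated figure, "a sample size of 160 patients (80 patients per group) would give 80% power", reproduces. It concerns 24 h opioid use and is not affected by this point. The article gives no power figure for the secondary scales, so d = 0.444 serves below only as an illustration.

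**2. Value of the screening score.** Adjusting for a baseline with correlation r to the outcome multiplies the residual variance by 1 − r². The article gives no r; 0.3 to 0.5 is assumed.

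| r | 1 − r² | 80 adjusted per group equals, unadjusted | power at d = 0.444 |
|---|---|---|---|
| 0 (unadjusted) | 1 | 80 | 80% |
| 0.3 | 0.91 | 80/0.91 = 88 | 84% |
| 0.5 | 0.75 | 80/0.75 = 107 | 90% |

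The gain equals 10% to 33% more patients.

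**3. What the 15% rule responds to.** In SD units, adding the baseline moves the estimate by about r × (chance difference in baseline means). That difference has SD √(2/80) = 0.158, so the shift has SD 0.047 at r = 0.3 and 0.079 at r = 0.5. Fifteen percent of 0.444 is 0.067. The chance of exceeding it is 2[1 − Φ(0.067/0.047)] = 16% at r = 0.3 and 2[1 − Φ(0.067/0.079)] = 40% at r = 0.5. This takes the threshold relative to the true effect. So the rule would more often than not leave out a useful score at this effect size, and admits it only when the groups happen to differ.

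**4. VAS: one common effect over six visits.** Assume an effect d at the four acute visits and none at the two late ones, equal visit variances, complete data, and a common between-visit correlation ρ. A common treatment effect is then the equally weighted mean, (4d + 0 + 0)/6 = 0.67d. The variance of a k-visit mean is (1 + (k − 1)ρ)/k, and SE = √(2 × variance/80). At ρ = 0.5:

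- Six visits: variance 3.5/6 = 0.583, SE 0.121, effect 0.296, power 69%.
- Four acute visits: variance 2.5/4 = 0.625, SE 0.125, effect 0.444, power 94%.

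At ρ = 0.3 the pair is 83% and 98%; at ρ = 0.7 it is 58% and 89%.

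**5. Sensitivity to the acute assumption.** The last dose is at 16 h, so 48 h is 32 h later, or 32/2.4 = 13 half-lives. If the effect is zero at 48 h as well, the acute average falls to 3/4 of d (0.333). At ρ = 0.5 its power is Φ(0.333/0.125 − 1.96) = 76%, not 94%. The six-visit average falls to 3/6 of d (0.222), with power Φ(0.222/0.121 − 1.96) = 45%.

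**6. The two lists of pain times.** The text gives 6, 12, 24 and 48 h; Table 1 gives 8 ± 4, 16 ± 4, 24 ± 4 and 48 ± 4 h. Six hours lies inside the first window (4 to 12 h). Twelve hours is the upper limit of the first and the lower limit of the second (12 to 20 h). The windows therefore do not settle which visit supplies the 12 h value. Only the Table 1 list brings late visits into the VAS model; the list in the text stops at 48 h.

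**The case against.** The strongest reply is that the sentence on the mixed model is condensed and is being read unfavourably. Much of this stands:

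- The per-visit models already give separate acute and late estimates; the mixed model is an addition.
- A mixed model across visits may contain treatment-by-time. The article does not exclude it, and such detail is commonly left to an analysis plan not shown here.
- KOOS JR and PROMIS-29 have no acute visit, so acute and late results cannot be mixed for them.
- The list of candidate covariates is open, so it is too strong to say that baseline scores will not be adjusted for. They are not named, and the stated rule is a poor way of admitting them.

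A reader might go further and infer that the plan enters the screening VAS as one of the responses, that a late effect is impossible given the half-life, or that an acute benefit would be missed. The documents support none of these. Nothing says the screening value is a response. The Background links poorly controlled acute pain to sensitization and chronic pain and describes dextromethorphan as mitigating sensitization, so a late effect has a stated rationale. And the per-visit models would still show an acute benefit.

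What survives is the covariate rule, which the article does state, and a repeated-measures sentence whose tested contrast cannot be identified.

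**Conclusion.** The point holds for secondary outcomes only. The screening scores are collected, none is a named covariate, and the stated rule selects on chance imbalance. The cost is precision, not bias: a variance factor of 0.91 to 0.75 is forgone if r is 0.3 to 0.5. That range is an assumption. For acute VAS the correlation may be weaker, since screening can fall up to 90 days before surgery.

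For VAS alone among the three scales, a single effect over the Table 1 visits would return 67% of a purely acute effect. This is conditional on three things: that the sentence means one common effect, that the model uses the Table 1 visits, and that the late effect is zero. The power figures also rest on an assumed effect size, the assumed ρ and a full effect at 48 h. They show the direction and rough scale of the loss; they do not forecast this trial.

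The primary 24 h opioid comparison and its sample size are unaffected. The change is worth making because it is free, not because the planned analysis is invalid.

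**What to change.** - Name the screening value of the same score as a prespecified covariate in the VAS, KOOS JR and PROMIS-29 models, whatever the 15% rule gives, and never as a post-treatment response.
- For VAS, include treatment-by-time. Report the acute contrast (to 48 h) separately from the week-6 and 3–6-month contrasts.
- Reconcile the pain times in the outcome definition (6, 12, 24, 48 h) with those in Table 1 (8, 16, 24, 48 h), and state which visits enter the acute contrast.

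The cost is analysis wording only, settled before unblinding. No new data, visits or patients are needed.

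### The 15% change-in-estimate rule selects adjustment covariates on chance imbalance, so the primary model is not fixed in advance and recovers only part of the precision that prespecified adjustment could give

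*Protocol article*

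**What the plan says.** The analysis paragraphs after Table 1 (Methods, Participants, interventions, and outcomes) compare opioid consumption between groups "using generalized linear models (GLM) with a Gaussian family specification, assuming the data are normally distributed". They add a model at each time point and a mixed model for repeated measures. The covariate rule follows: "Confounders will be defined as variables, which, when added to the model, alter the effect estimate". The threshold is a change above 15%. The next sentence gives the candidates: "Potential a priori confounders include body mass index (BMI), sex, age, race, and American Society of Anesthesia (ASA) grade". No covariate is fixed in any model, and the text does not say whether variables are tried singly, forward or backward.

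Assignment of interventions describes randomisation "with a 1:1 treatment allocation ratio and no stratification factors". The sample-size paragraph plans an unadjusted comparison of means: "a sample size of 160 patients (80 patients per group) would give 80% power to detect a difference in postoperative opioid consumption". Alpha there is 0.05, two-sided.

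**The concern.** Change-in-estimate selection belongs to observational studies, where a baseline variable can be systematically related to exposure. Randomisation removes that relation by design. Here the rule has three effects.

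- **It selects on the wrong quantity.** A strongly prognostic covariate that happens to be balanced barely moves the estimate and is left out, although it would reduce the residual variance. A weaker covariate that happens to be imbalanced can enter.
- **The threshold depends on the result.** It is 15% of the observed treatment effect, so it is easier to cross when the effect is small.
- **It does not define one model.** The covariate set can differ between outcomes and time points, and between two analysts who order the steps differently.

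At stake are a primary estimate that is settled before the data are seen, and some precision in a trial planned at 80% power with no surplus.

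**Working it through.** **Inputs from the article.** Difference 2.4, SD 5.4, 80 per group, two-sided alpha 0.05, power 80%, five named candidates, 1:1 unstratified allocation.

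**Assumption.** The share of outcome variance that the covariates jointly explain (R²) is not given. The range used is 0 to 0.3.

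**1. The plan's own figure.** d = 2.4/5.4 = 0.444. By the normal approximation, n per group = 2(1.960 + 0.842)²/0.444² = 79.5, so 80, with power 80.3%. By the noncentral t method that the article cites, the requirement is 80.4 per group and power at 80 is 79.8%. The stated size reproduces, for an unadjusted comparison.

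**2. How the threshold moves.** At the planned effect it is 0.15 × 2.4 = 0.36. If the observed difference were 0.2 (an illustration), it would be 0.15 × 0.2 = 0.03.

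**3. Selection.** Simulation: 80 per arm, five independent standard-normal covariates sharing R² equally, and each covariate tested singly against the unadjusted estimate. The ranges cover several independent runs of 3,000 to 6,000 trials per setting, at R² 0.05–0.30.

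- No effect: at least one covariate enters in 72–96% of trials. The average number entered is 1.8 of 5 at R² 0.05 and 3.2 of 5 at R² 0.30.
- Planned effect (d = 0.444): at least one enters in 12–45%.

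**4. Type I error under the rule.** 4.1–5.6% across runs.

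**5. Power at d = 0.444 (%).** Each row is one run.

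| R² | Unadjusted | 15% rule | All five fixed | Fixed minus rule |
|---|---|---|---|---|
| 0 | 80.4 | 80.4 | 78.3 | −2.1 |
| 0 (second run) | 80.1 | 80.2 | 79.0 | −1.2 |
| 0.03 | 79.6 | 79.9 | 79.6 | −0.3 |
| 0.05 | 79.6 | 80.4 | 80.4 | 0.0 |
| 0.10 | 80.0 | 81.4 | 83.1 | 1.7 |
| 0.20 | 78.5 | 82.6 | 87.1 | 4.5 |
| 0.30 | 80.2 | 85.1 | 90.5 | 5.4 |

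Further runs gave a difference of 0.8–1.8 points at R² 0.10, 4.0–4.4 at 0.20 and 5.2–5.4 at 0.30. With 3,000 trials the Monte Carlo standard error of a power near 80% is √(0.8 × 0.2/3000) = 0.7 points.

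As a check, effect d/√(1 − R²) in the t-test formula, ignoring the degrees of freedom spent, gives 83.8%, 87.8% and 91.6% at R² 0.1, 0.2 and 0.3. Fixed adjustment breaks even with no adjustment near R² = 5/158 = 0.03.

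**6. Ambiguity of the rule.** Single, forward and backward versions were applied to the same simulated trials at d = 0.444. The ranges cover two separate simulations of the three versions (3,000 and 1,500 trials per setting).

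| R² | Versions choose different covariate sets | Versions disagree on p < 0.05 |
|---|---|---|
| 0.1 | 11–25% | 1.3–3.1% |
| 0.2 | 21–38% | 2.7–3.9% |
| 0.3 | 26–48% | 4.1–5.8% |

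**7. Bias.** Under the rule the mean estimate drifted slightly from zero: 0.448–0.455 against a true 0.444 at R² 0.1–0.3.

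**The case against.** The strongest reply is that little harm is shown, and much of it stands.

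- **Inflated false-positive rate.** A reader might infer this from data-driven selection. The simulations do not support it: type I error stayed near 5% for a single version, and was at most 6.0% when the most favourable of three versions was taken.
- **Power below plan.** A reader might infer that the rule pushes power under the planned 80%. It does not: in every one-at-a-time run it matched or exceeded the unadjusted comparison on which the sample size rests. What is lost is a gain the sponsor did not plan for, and only if the covariates are prognostic. The article gives no evidence on that.
- **Selecting everything or nothing.** That would overstate the erratic selection. Under no effect about two to three of five covariates enter on average, and at the planned effect selection is not rare.
- **Scope.** The sentence on the primary aim names no covariates, and the rule appears after the repeated-measures sentence. An unadjusted primary analysis with a confounder check is a possible reading. But the text does not say so and restricts the rule to no analysis, so the ambiguity is part of the fault.
- **Unblinding.** The rule needs group codes, not knowledge of which code is active. So the claim is only that the model depends on outcome data by group.
- **Candidates named beforehand.** This narrows the choice, but the words *potential* and *include* leave the list open, and entry is still decided by the treatment estimate.
- **Alternative remedy.** Declaring the primary analysis unadjusted would also settle the model and match the sample size. It would forgo the possible precision.

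A separate analysis plan may exist. It would not cure a rule that the protocol states, and a plan written to this text would inherit it.

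**Conclusion.** The point stands on prespecification and forgone precision. The stated rule is unsuited to a randomised trial: it leaves the primary model dependent on outcome data by group, allows it to vary by outcome and by implementation, and ignores prognostic strength. The forgone power against fixed adjustment is about 1–2 points at R² 0.1, about 4–6 points at R² 0.2–0.3 and nil at about 0.05 or less. At R² 0 fixed adjustment instead costs about 1–2 points.

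These sizes rest on an assumed R², five independent normal covariates of equal strength, a Gaussian outcome, no dropout and one-at-a-time selection. Race and ASA grade are categorical and would use more degrees of freedom than was simulated. The change should be made, but the rule does not threaten the trial's validity.

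**What to change.** - Delete the 15% rule.
- Define the primary model as treatment plus a short, closed set of prognostic baseline covariates from those already listed, for example age, sex, BMI and ASA grade. Enter them regardless of any observed change in the estimate or p-value.
- For VAS pain, KOOS JR and PROMIS-29, add the baseline value of the outcome, which Table 1 already collects at screening.
- Report the unadjusted estimate, which matches the sample-size basis, as a sensitivity analysis.

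The cost is a wording change made before outcome data by group are examined, a few degrees of freedom out of 160, and a small loss of power if the covariates prove not to be prognostic. No new data are needed.

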**Methods:**

This is a single-center, multi-dose, randomized, double-blinded, placebo-controlled trial. A total of 160 participants will be randomized 1:1 to receive either 60 mg oral dextromethorphan hydrobromide preoperatively, as well as 30 mg 8 h and 16 h postoperatively, or matching placebo. Outcome data will be obtained at baseline, during the first 48 h, and the first two follow-up visits. The primary outcome measure will be total opioid consumption at 24 h postoperatively. Secondary outcomes related to pain, function, and quality of life will be evaluated using standard pain scales, the Knee Injury and Osteoarthritis Outcome Score for Joint Replacement (KOOS, JR) questionnaire, the Patient-Reported Outcomes Measurement Information System (PROMIS-29) questionnaire, and clinical anchors.

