## Methods

### Participants, interventions, and outcomes

This is a single-center, multi-dose, randomized, double-blinded, placebo-controlled trial to evaluate the efficacy of perioperative dextromethorphan compared to placebo for postoperative pain in patients undergoing TKA. All standard of care interventions related to TKA are permitted during the trial. Patients aged 18 or older planning to undergo TKA will be screened for eligibility, as outlined in figure (Fig. 1). Those who meet inclusion/exclusion criteria and decide to participate will sign an informed consent prior to randomization. Patients randomized to the treatment group (*n* = 80) will receive 60 mg oral (pill) dextromethorphan hydrobromide preoperatively, as well as 30 mg 8 and 16 h postoperatively. Patients randomized to the control group (*n* = 80) will receive analogous oral placebo at the same time points.

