**Fig. 1 Fig1:**
[figure not shown]
Study design flowchart. TKA = total knee arthroplasty; AEs = adverse events; VAS = visual analog scale; KOOS JR = Knee injury and Osteoarthritis Outcome Score for Joint Replacement; PROMIS = Patient-Reported Outcomes Measurement Information System

A standardized, multimodal anesthetic protocol will be implemented. Preoperatively, patients will receive up to 400 mg celecoxib and 1000 mg acetaminophen. Intraoperative anesthetics will include spinal-epidural (15 mg bupivacaine) and propofol (75–100 µg/kg/min titrated to sedation). In the inpatient postoperative setting, oral oxycodone will be available as needed. All pain medications may be adjusted as indicated. All such adjustments will be logged and reported with the final published results.

Participants have the right to withdraw at any point during the course of the study without prejudice. Additionally, the investigator can discontinue participants at any time if medically necessary. Participants may also be withdrawn from the study for the following reasons: (1) concerns for patient safety, (2) noncompliance with study procedures or obligations, or (3) patient withdrawal of consent. In the event that a patient withdraws due to an adverse event thought to be at least possibly related to study treatment, they will be followed until the adverse event resolves or the patient is deemed medically stable by the Principal Investigator. All findings will be documented.

To ensure adherence to intervention protocols, the study drug or placebo will only be administered while the patient is hospitalized for their standard of care treatment. During this time, patients will receive extensive monitoring that is comparable to (or better than) what the standard patient receives when hospitalized for acute medical illness, including a nursing ratio that is equal to or better than 4:1. In addition, dedicated research staff and investigators will be available to ensure all interventions are administered appropriately.

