The primary outcome will be the mean difference in postoperative opioid consumption (morphine equivalents) at 24 h. Secondary outcomes include mean subjective postoperative pain at 6, 12, 24, and 48 h after surgery, as measured using VAS (or equivalent NRS) with and without movement preoperatively; mean postoperative opioid consumption at 48 h; mean long-term pain and function, as measured using the pathology-specific KOOS, JR; mean overall subjective status, as measured using the 29 question PROMIS-29 questionnaire; and subjective improvement, as measured using clinical anchors for pain and overall improvement. Details regarding enrollment, interventions, assessments, visits, and when specific outcomes are obtained can be found in Table 1. In addition to efficacy outcomes, this study has several exploratory objectives, which may be reported independently from the main study results. The first of these exploratory aims is to assess whether baseline factors (e.g., poor physical function, anxiety, depression, fatigue, sleep disturbance) are associated with a differential response relationship to dextromethorphan. Second, we will plan to perform a retrospective review to assess whether dextromethorphan has an effect on the anesthetic course.

**Table 1 Tab1:** Study calendar: Screening activities may be performed any day up to and including day 1 on study, but will always be performed prior to administration of study drug or placebo. POD1 = post-op day 1; KOOS JR = Knee injury and Osteoarthritis Outcome Score for Joint Replacement; PROMIS = Patient-Reported Outcomes Measurement Information System; 1 = As clinically indicated. A symptom-directed physical exam to be completed for AEs which are at least possibly related to study treatment

**Study procedure**	**Screening** **(day − 90)**	**Day 1**				**48 ± 4 h**	**Week 6 ± 3**	**Final** **(3–6 months)**
		**Pre-op**	**8 ± 4 h**	**16 ± 4 h**	**24 ± 4 h**			

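### The per-protocol set for a 24 h primary outcome requires attendance at visits out to 3–6 months, so fully dosed patients with complete primary data are dropped for later non-attendance

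*Protocol article*

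**What the plan says.** All references are to the Methods of the protocol article.

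- **Per-protocol definition** (statistical text after Table 1): only protocol-adherent participants are included, "as defined by their having received all assigned treatments and completed all follow-up visits". This is the only definition given, and it is not varied by outcome.
- **Primary outcome** (outcomes paragraph before Table 1): "The primary outcome will be the mean difference in postoperative opioid consumption (morphine equivalents) at 24 h".
- **Dosing** (Participants, interventions, and outcomes): "60 mg oral (pill) dextromethorphan hydrobromide preoperatively, as well as 30 mg 8 and 16 h postoperatively". The adherence paragraph adds that "the study drug or placebo will only be administered while the patient is hospitalized for their standard of care treatment".
- **Visits** (Table 1): after the 24 h assessment come 48 ± 4 h, week 6 ± 3 and a final visit at 3–6 months. The Abstract uses the term follow-up visits for those beyond the first two days: "Outcome data will be obtained at baseline, during the first 48 h, and the first two follow-up visits".
- **Primary analysis set** (statistical text after Table 1): "The analysis for the primary outcomes will be by intention-to-treat (ITT"). The per-protocol analysis is announced as an addition to it.

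**The concern.** A per-protocol analysis is meant to show the contrast among patients who received treatment as assigned. For the 24 h outcome, everything relevant to that has happened by 24 h: the doses have been given in hospital and the opioid use has been counted. Attendance weeks or months later cannot change either.

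The visit condition therefore makes the set no more adherent for this outcome. It discards valid primary data and selects patients on an event that follows randomisation, treatment and the outcome itself. If attendance is related to early pain, opioid use or recovery, and this works differently in the two arms, the selection can shift the per-protocol contrast. A difference from the intention-to-treat result could then reflect missed doses or late attrition, and the reader would have to separate the two.

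**Working it through.** **1. Timeline against the definition.**

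| Event | Time | Needed for the 24 h outcome? |
|---|---|---|
| Dose 1 | before surgery | yes |
| Doses 2 and 3 | 8 h and 16 h | yes |
| Opioid consumption, primary | 24 h | yes |
| 48 h assessment | 48 ± 4 h | no |
| First later visit | week 6 ± 3 | no |
| Final visit | 3–6 months | no |

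Whether or not the 48 h assessment counts as a follow-up visit, the week 6 and 3–6 month visits do. A patient who meets all three rows marked yes and misses either of those visits fails the definition.

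**2. The plan's own sample size.** Inputs from the sample-size paragraph: difference 2.4, SD 5.4, two-sided alpha 0.05, 80 per group.

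- Standardised effect: d = 2.4/5.4 = 0.444.
- Noncentrality: d × √(n/2) = 0.444 × √40 = 2.81, with 158 degrees of freedom.
- Power: 79.8% by noncentral t (80.3% by normal approximation). The stated 80% is reproduced.

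**3. Loss from the visit condition alone.** The same paragraph anticipates 5–10% dropout. Assume that all of it falls after 24 h, equally in both arms, with every dose taken and all 24 h data present.

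| Late loss | Per group | Total | d × √(n/2) | Power, noncentral t |
|---|---|---|---|---|
| 0% | 80 | 160 | 2.81 | 79.8% |
| 5% | 80 × 0.95 = 76 | 152 | 2.74 | 77.7% |
| 10% | 80 × 0.90 = 72 | 144 | 2.67 | 75.4% |

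With membership defined on doses and 24 h data only, the same late loss removes nobody and the set stays at 160.

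**4. Possible bias, as an illustration.** Suppose there is no true effect, and that 24 h opioid use has correlation ρ with a normally distributed tendency to miss later visits. If a fraction p of an arm is lost, the mean of those retained shifts by −ρ × 5.4 × φ(z)/(1 − p), where z is the (1 − p) normal quantile and φ the normal density.

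- p = 5%: φ(z)/(1 − p) = 0.103/0.95 = 0.109.
- p = 15%: φ(z)/(1 − p) = 0.233/0.85 = 0.274.
- Active (15% lost) minus control (5% lost): −ρ × 5.4 × (0.274 − 0.109) = −ρ × 5.4 × 0.166, before rounding of the terms.
- ρ = 0.2 gives −0.18; ρ = 0.4 gives −0.36.

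Against the planned difference of 2.4, these are 0.18/2.4 = 7.5% and 0.36/2.4 = 15%. The shift is zero if ρ = 0, or if loss is equal in both arms and works the same way. The correlations and the 5% versus 15% split are assumptions; the protocol article gives no figures for them.

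**The case against.** The strongest reply is that little depends on this analysis. The trial tests superiority, the primary analysis is by intention to treat, and no success criterion or sample size rests on the per-protocol set. Sensitivity analyses with imputation are planned as well. All of this is correct, and it limits the importance of the point.

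A second reply is that visit completion matters for outcomes collected at week 6 and 3–6 months, such as KOOS, JR, PROMIS-29 and the clinical anchors, and that outcome-specific sets are often left to an analysis plan. The first half stands for those outcomes. It argues for a definition that varies by outcome, not for one rule applied to the 24 h result. The article does not list the outcomes that the per-protocol analysis covers. However, the definition comes directly after the plan for the primary outcome and carries no restriction, so applying it there is the natural reading. The point concerns a rule that is stated, not a detail left out.

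Third, any set that requires all doses is already selected, because treatment is stopped for certain adverse events and dose completion may differ by arm. This is true, and the fix below does not remove it. It removes only the extra selection that has no link to dosing.

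Stronger readings are tempting, but the documents do not support them:

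- **Larger loss.** At 20% late loss the set would be 128 and power 70.4%. That rate is above the protocol's own 5–10%.
- **Bias of about a quarter of the effect.** If 10% of one arm were lost and differed from the rest by a full SD, that arm's mean would move by 0.10 SD, and 0.10/0.444 = 23% of the planned effect. Nothing in the article suggests a difference that large or confined to one arm.
- **A per-protocol result that cannot be interpreted.** It would be harder to interpret, but the number excluded only for late visits could be tabulated by arm.

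**Conclusion.** The point holds for the supportive per-protocol analysis of the primary outcome. Applied as written, the definition excludes patients with all doses and complete 24 h opioid data because of later non-attendance.

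At the protocol's own dropout range, the cost is 8 to 16 patients and roughly 2 to 4 percentage points of power. This assumes that all dropout falls after 24 h; if some falls earlier, less of the loss is due to the visit condition. Power is only a rough measure here, since the trial was not sized on this analysis.

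Bias is possible but not shown. It needs late loss that is related to 24 h opioid use and that differs between arms in amount or in mechanism. A reader might infer that the trial's main conclusion is at risk. It is not, because the intention-to-treat result does not use this set. The problem is worth correcting because the condition adds nothing for this outcome and is easy to change.

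**What to change.** Replace the single definition with one by outcome: a participant belongs to the per-protocol set for an outcome if all assigned doses were received and that outcome was observed at its assessment time. For the primary outcome this means all three doses and opioid data to 24 h. Require attendance at the week 6 and 3–6 month visits only for outcomes measured at those visits.

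No further condition is needed. In particular, a clause about major deviations would bring in a term that the article does not define.

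The cost is one sentence and one analysis flag per outcome, with no new data. Make the change before unblinding. If the full protocol or analysis plan already defines the set by outcome, bring the published definition into line with it.
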